## Abstract

**Background:**

Liver transplantation is the definitive treatment for many end-stage liver diseases. However, the life-long immunosuppression needed to prevent graft rejection causes clinically significant side effects. Cellular immunomodulatory therapies may allow the dose of immunosuppressive drugs to be reduced. In the current protocol, we propose to complement immunosuppressive pharmacotherapy with third-party multipotent adult progenitor cells (MAPCs), a culture-selected population of adult adherent stem cells derived from bone marrow that has been shown to display potent immunomodulatory and regenerative properties. In animal models, MAPCs reduce the need for pharmacological immunosuppression after experimental solid organ transplantation and regenerate damaged organs.

**Methods:**

Patients enrolled in this phase I, single-arm, single-center safety and feasibility study (n = 3-24) will receive 2 doses of third-party MAPCs after liver transplantation, on days 1 and 3, in addition to a calcineurin-inhibitor-free "bottom-up" immunosuppressive regimen with basiliximab, mycophenolic acid, and steroids. The study objective is to evaluate the safety and clinical feasibility of MAPC administration in this patient cohort. The primary endpoint of the study is safety, assessed by standardized dose-limiting toxicity events. One secondary endpoint is the time until first biopsy-proven acute rejection, in order to collect first evidence of efficacy. Dose escalation (150, 300, 450, and 600 million MAPCs) will be done according to a 3 + 3 classical escalation design (4 groups of 3-6 patients each).

**Discussion:**

If MAPCs are safe for patients undergoing liver transplantation in this study, a phase II/III trial will be conducted to assess their clinical efficacy.

## Background

### Liver Transplantation

Liver transplantation remains the only definitive treatment for a number of diseases, including end-stage chronic liver disease, acute liver failure, or limited hepatic neoplasms, with patient and graft survival rates exceeding 75% after five years [1,2]. However, liver transplantation is burdened by the need for life-long immunosuppression in order to prevent graft rejection. All drugs currently used for immunosuppression cause significant clinical side effects. Besides their well-known intrinsic toxicities (e.g., neurotoxicity of tacrolimus and renal toxicity of ciclosporin [3-5]), they also increase the risk for cancer and opportunistic infections [6-11]. The long-term overall success of liver transplantation is frequently determined by complications related to immunosuppressive drug therapy. Yet, immunosuppressants are indispensable to maintain graft function and to cover aberrations in immune reactions that may result in rejection of the transplanted organ.

Growing numbers of patients in need of a liver graft are faced with a continuous shortage of donor organs. In the Eurotransplant area, for instance, only 1631 transplant livers were available for 2641 patients on the waiting list in 2009 [12]. To overcome this shortage, criteria for the acceptance of donors have been liberalized, e.g., in terms of prolonged ischemia time, increased donor age, or the presence of clinically significant donor liver steatosis. While increasing the donor pool, these "marginal" organs are also associated with higher incidences of primary graft dysfunction and major complications [13-15]. Here, we propose a novel protocol involving treatment of liver transplant recipients with multipotent adult progenitor cells (MAPCs) with the goal of reducing the dose of immunosuppressive drugs and of supporting liver regeneration in marginal grafts.

### Multipotent adult progenitor cells

MAPCs belong to the family of mesenchymal stem cells (MSCs) and are cultured from bone marrow aspirates [16-18]. The clinical-grade MAPC product (MultiStem^®^, Athersys Inc., Cleveland, Ohio, USA) to be used in this study is isolated from a single bone marrow aspirate and cultured with heat inactivated fetal bovine serum (FBS) and growth factors EGF and PDGF. Cells display a linear expansion rate to 65 population doublings or greater before senescence. Doubling times average 20 hours during expansion. Cells are used after 30 population doublings and tested by flow cytometry, in vitro immunomodulatory assays and cytogenetics. Moreover, extensive safety testing in immunodeficient animal models is performed [19-21].

MAPCs share immunosuppressive functions with MSCs [16], they have been shown to suppress T-cell proliferation in vitro and ameliorate graft-versus-host disease (GvHD) in small animal models [22]. First clinical trials with MAPCs have already been initiated to treat GvHD and Crohn's disease [21]. Moreover, MAPCs have regenerative properties, contributing to vascular regeneration in models of limb ischemia [23], improving cardiac function after myocardial infarction [24], and contributing to the regeneration of injured livers through their ability to differentiate into hepatocyte-like cells [25].

MSCs and MAPCs have been successfully applied in preclinical heart transplantation models in combination with various immunosuppressants [26-29]. Our group has demonstrated that MSCs and MAPCs induce long-term graft acceptance when applied together with mycophenolic acid [26,27]. In contrast, calcineurin inhibitors (CNIs) have been shown to abrogate the immunosuppressive effect of MSC therapy in this and other animal models [30]. The current study protocol therefore calls for a CNI-free, "bottom-up" immunosuppressive regimen combined with the MAPC infusions.

### "Bottom-up" immunosuppression

Current standard clinical protocols for post-transplant immunosuppression vary between institutions, continents and indications. However, most induction therapies include corticosteroids that are subsequently tapered over the first months. CNIs, such as ciclosporin A or tacrolimus, are the mainstay of immunosuppression, sometimes in combination with mycophenolic acid (MPA). Further treatment options are also available, like e.g. thymoglobulin. In addition, anti-CD25 monoclonal antibodies can be used to block activated T cells in the first week after the operation [31]. Because standard immunosuppressive treatment is often reliant on CNI-based regimens, which can cause among other things renal impairment, hypertension, and hyperglycemia [32-35], efforts have been made to reduce CNI exposure for liver transplant recipients [36]. Indeed, a proportion of patients can achieve graft acceptance without CNIs, while acute rejection episodes in the remaining patients can be treated with high-dose steroids and intensification of the baseline immunosuppressive regimen, without graft loss.

"Bottom-up" immunosuppression, then, refers to a CNI-free induction protocol consisting of steroids, mycophenolic acid and basiliximab. CNIs are introduced only when needed, e.g. in case of biopsy-proven acute rejection. This approach is feasible in liver transplantation, because of its lower immunogenicity in comparison to other types of organ transplants and because of the low risk of graft loss or permanent graft damage by acute rejection episodes. The "bottom-up" regimen has already been applied successfully in clinical studies [37,38] and is particularly valuable for high-MELD (Model for End-stage Liver Disease) patients with increased risk of infections or renal dysfunction. In view of the synergistic interplay of MSCs with mycophenolic acid, and because CNIs have been shown to abolish the beneficial effect of MSCs in animal models, this study will use "bottom-up" immunosuppression in combination with MAPCs. We hypothesize that MAPC infusions will help to significantly delay the introduction of CNIs or allow to avoid them altogether.

## Methods & Design

### Objectives and Endpoints

The primary objective of this study is to assess the safety of MAPC infusions in patients undergoing liver transplantation. The secondary objective is to provide preliminary evidence regarding the study product's efficacy by analyzing the time to first biopsy-proven acute rejection up to day 90. Furthermore the incidence of malignancies or any other unexpected side effects until day 365 will be investigated. After closing this study, all participants will be enrolled in a follow-up protocol that assesses long-term safety of MAPCs over an additional 6 years. This two-step follow-up approach has been designed in close collaboration with the responsible regulatory authorities. Immunomonitoring will be performed on blood samples from all participating patients to assess the anti-donor immune response, the composition of circulating T cell subpopulations, the anti-donor antibody response and to identify a putative biomarker signature that is associated with transplant tolerance.

### Study Design

This is a phase I, single-arm, single-center safety and feasibility study based on a classical 3 + 3 dose escalation design. Safety of MAPC infusions is assessed by the occurrence of a dose-limiting toxicity (DLT) event (Figure 1) within 30 days after administration of the first MAPC dose. Because the focus in this study is on safety, a conservative dose escalation scheme rather than an accelerated titration design was chosen. The starting dose of 2 × 150 million MAPCs (MultiStem^®^) per patient has already been administered to patients for various indications, with no side effects observed so far. This dose corresponds to doses that have been shown to prolong graft survival in animal models. The maximum dose of 2 × 600 million MAPCs is still at least 50% lower than the maximum-tolerated dose in laboratory animals and similar to MSC doses already injected into patients [39].

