**Figure 1 F1:**
[figure not shown]
**Dose-limiting toxicity (DLT) events.**Clinical events of toxicity related to MAPC infusions. If more than one DLT event occurs in a dose cohort, the study will be stopped.

Each patient will receive 2 doses of MAPCs. The first dose will be administered during liver transplantation directly into the portal vein after graft reperfusion. As the study begins with liver transplantation this day is defined as day 1 (in contrast to most preclinical investigation that defines the day of the transplant as "day 0"). The second dose will be administered intravenously on day 3 in the intensive care unit. Three patients will be treated with the starting dose of 2 × 150 million third-party MAPCs. If no DLT is observed in any of the 3 patients of this cohort, the second cohort of 3 patients will be treated with 2 × 300 million MAPCs, continuing with the third cohort with 2 × 450 million MAPCs and the fourth cohort with a final dose of 2 × 600 million MAPCs. The dose escalation design is illustrated in Figure 2.

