#### Follow-up

Thirteen follow-up visits will be performed during the first 30 days after transplantation. Blood samples will be collected, clinical examinations performed, and adverse events recorded as detailed in Table 1. Dose-limiting toxicity (DLT) assessments will be performed on days 1, 2, 3, 4, 10, and 30. Per protocol, biopsies will be performed during liver transplantation and on days 4 and 10, with additional biopsies obtained whenever clinically necessary. Four additional outpatient visits are planned to further evaluate the study patients (including screening for malignancies) until day 365 (Table 1). Additional blood samples will be obtained to investigate surrogate markers of the patient's immune response status. This translational immunomonitoring will be performed on days 1, 3, 10, and 30, including mixed lymphocyte reactions to evaluate anti-donor reactivity, flow cytometry to describe the recipients' leucocyte repertoire, serum analysis to screen for anti-donor antibodies and cytokines. Moreover, we will analyze peripheral blood samples for genes that have recently been associated with tolerance in liver and kidney transplantation such as CKLRF1, CLIC3 and TOAG-1 [44-48]. Using specific donor characteristic (e.g. differences in gender or MHC haplotypes) circulating MAPC will be tracked in blood samples by rtPCR. Further labeling of transfused MAPC is not planned at this stage for safety reasons. We expect MAPC to be cleared quickly from the recipient because they have been susceptible to NK-cell lysis and were detected only transiently in most animal experiments [49].

**Table 1 T1:** Assessment schedule.

Study Phase	LTx		EOT	Post-Treatment Phase						Follow-Up			
**Visit no**.	**1**	**2**	**3**	**4**	**5-9**	**10**	**11**	**12**	**13**	**14**	**15**	**16**	**17**

Study days	1	2	3	4	5-9	10	14	20	30 ± 10 d	90 ± 30 d	180 ± 30 d	270 ± 30 d	365 ± 30 d

MAPC treatment	X		X										

DLT assessment	X	X	X	X		X			X				

Laboratory	X	X	X	X	X	X	X	X	X	X	X	X	X

Doppler ultrasound	X	X	X	X		X			X	X			X

Liver biopsy	X			X		X							

Immunomonitoring	X		X			X			X				X

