### Data safety monitoring committee

An independent data safety monitoring committee will be installed to monitor the study progress. The committee will include basic scientists and clinicians not otherwise involved in the trail. Members of this group will review the clinical and investigational data to ensure that participants are not exposed to undue risk. The data safety monitoring committee will review the data up to day 30 for each dosing cohort and will then give written recommendation on whether or not to continue the study. Members of the committee will also recommend on whether the next dosing cohort should start enrolment or whether the current cohort should be expanded. The data safety monitoring committee can recommend stoppage of the study for reasons of patient safety at any time. Whenever adverse events occur, the principal investigator and the study team will communicate those to the data safety monitoring committee in due time. If an adverse event is serious (SAE) or unexpected (SUSAR), the responsible authorities will be informed. About 10 SAEs might be expected in each liver transplant recipient transplanted with high MELD score during the first 30 days.

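### The closing DLT assessment may be done as early as day 20, so the visit schedule does not secure the 30-day DLT endpoint that drives escalation

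*Protocol article*

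**What the plan says.** The Study Design section of the protocol article defines the primary safety endpoint as a DLT occurring "within 30 days after administration of the first MAPC dose". The same section fixes the day count: "As the study begins with liver transplantation this day is defined as day 1". The first infusion is given during the transplant. For the other infusion, "The second dose will be administered intravenously on day 3 in the intensive care unit".

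The Follow-up section says that DLT "assessments will be performed on days 1, 2, 3, 4, 10, and 30". It also states: "Thirteen follow-up visits will be performed during the first 30 days after transplantation". Table 1 in that section is looser, because it gives visit 13, the last with a DLT assessment, as day 30 ± 10. In Table 1 the DLT and Doppler rows are both blank at visits 5-9, 11 and 12. After visit 13 the next Doppler is at visit 14, day 90 ± 30.

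The section on dose-limiting toxicity makes Doppler ultrasound the means of detecting toxicity from the intraportal infusion (portal flow, resistive index of the hepatic artery, occlusion, changed flow patterns).

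The section on the data safety monitoring committee says that the committee "will review the data up to day 30 for each dosing cohort and will then give written recommendation". The recommendation covers continuing the study, opening the next cohort or expanding the current one. Adverse events are also passed to the committee as they occur.

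**The concern.** The endpoint window, the tolerance of the visit that closes it and the data cut for the escalation decision are all stated, and they do not fit together. A site that sees a patient on day 20 complies with Table 1, yet the last scheduled DLT assessment is then well short of the end of the window. Nothing in the article requires visit 13 to be at or after the end of the window, or to be completed in every cohort patient before the committee recommends.

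The cohorts are small, so one missed event changes the decision. It turns 1 of 3 (expand) into 0 of 3 (escalate), or 2 of 6 (close the study) into 1 of 6 (escalate). A missed DLT can only push towards escalation, in a design that the authors chose because it is conservative. An analysis plan cannot recover an assessment that was never made.

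**Working it through.** **The plan's own figure.** Four levels of 3 patients give 4 × 3 = 12, and four levels of 6 give 4 × 6 = 24. The minimum is one cohort of 3 that stops at the first level. This reproduces the stated 3 to 24 patients with 12 as the optimal case, so the escalation rule used below is read as the authors intend.

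**Day count.** The first dose is on day 1, so days since the first dose = study day − 1, and the 30-day window ends on study day 31. Visit 13 may fall from day 30 − 10 = 20 to day 30 + 10 = 40.

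| Visit 13 on day | Days after first dose | Days after second dose | Window days with no later scheduled DLT assessment |
|---|---|---|---|
| 20 | 19 | 17 | 30 − 19 = 11 (11/30 = 37%) |
| 30 | 29 | 27 | 1 |
| 31 | 30 | 28 | 0 |
| 40 | 39 | 37 | 0 |

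Day 20 is also the nominal day of visit 12. If visit 13 is done on day 20, the next scheduled Doppler is visit 14, on day 90 − 30 = 60 at the earliest.

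**The committee's cut, under its two readings.**

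- *Day 30 is a calendar cut.* After an early visit 13, the committee still has adverse events up to day 30, but no scheduled Doppler or DLT assessment after day 20. With a visit 13 after day 30, the last DLT assessment under review is day 10.
- *Day 30 is the label of visit 13.* A late visit is waited for, so nothing is lost at that end. An early visit still closes scheduled DLT assessment at day 20.

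The Doppler gap after an early visit exists under both readings. The late-visit problem exists only under the first.

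**Effect on the escalation rule.** A level is passed with 0 of 3, or with 1 of 3 followed by 0 of 3:

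P(escalate) = (1 − p)³ + 3p(1 − p)² × (1 − p)³

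The article gives neither a DLT rate nor DLT timing, so p is an assumed range. The two right-hand columns assume that every visit 13 falls on day 20 and that no later DLT is captured. The observed risk is then 0.9p if 90% of DLTs come before day 20, or 1 − (1 − p)^(19/30) under a constant hazard over 30 days.

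| True 30-day risk p | Full window | 90% before day 20 | Constant hazard |
|---|---|---|---|
| 10% | 0.91 | 0.92 | 0.96 |
| 20% | 0.71 | 0.75 | 0.85 |
| 30% | 0.49 | 0.56 | 0.70 |
| 40% | 0.31 | 0.38 | 0.54 |
| 50% | 0.17 | 0.23 | 0.39 |

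Worked line for p = 20%:

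- Full window: 0.8³ = 0.512, and 3 × 0.2 × 0.8² × 0.512 = 0.197; the sum is 0.71.
- 90% before day 20: the observed risk is 0.18, giving 0.75.
- Constant hazard: the observed risk is 1 − 0.8^(19/30) = 0.132, giving 0.85.

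**The case against.** The strongest reply is that the endpoint is the occurrence of an event and not a tick at a visit. Patients are examined and adverse events recorded at the other visits too, and adverse events go to the committee as they happen. A reintubation, pulmonary embolism or shock on day 25 would be reported whether or not a DLT form was due. This stands, and it narrows the exposure mainly to findings that only a scheduled Doppler would show.

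The toxicities described are also tied to the infusion (embolism in the first capillary bed, lung injury, anaphylaxis), the cells are expected to clear quickly, and the assessments are dense on days 1 to 4 accordingly. Late DLTs are probably few. This stands as well. A reader might spread late DLTs evenly over days 11 to 31 and conclude that a day-20 visit misses 11/21 = 52% of them. The document gives no support for even spacing, so that figure should not be used.

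A reader might also infer that early and late visits both bias every cohort towards escalation. The document does not support this: the late-visit gap needs day 30 to be a calendar cut, and on the other reading the committee waits for the visit. Nor do unequal assessment times make DLT proportions incomparable across levels, since this 3 + 3 rule applies fixed counts within a level and compares no proportions. The day 30 versus day 31 difference is trivial by itself.

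Finally, committee procedure is often left to the full protocol, which is not shown. That does not remove the point, because it rests on what the article states about the endpoint, the visit tolerance and the data cut.

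**Conclusion.** The point holds in a limited form and should be fixed; it does not undermine the 3 + 3 design. The visit 13 tolerance allows the only DLT assessment and Doppler scheduled after day 10 and before visit 14 to take place up to 11 days (37%) before the 30-day window ends. DLTs seen only on Doppler could then be missed before an escalation decision. Whether a late visit 13 must be available to the committee is unsettled.

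The size is uncertain, because the DLT rate and timing are not given and the DLT definitions in Figure 1 are not shown. At an assumed 20% risk, P(escalate) rises from 0.71 to 0.75 with 90% of DLTs before day 20, and to 0.85 under a constant hazard. Both assume that every visit falls on day 20 and that all later DLTs are lost. Since clinically evident events are reported anyway, 0.85 is an upper-range illustration. The stronger conclusion, that cohorts will be declared free of DLTs on incomplete data, does not follow. The schedule permits that outcome but does not require it.

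**What to change.** - Use one endpoint cut in the Study Design, Follow-up (with Table 1) and committee sections: either 30 days after the first dose, which is study day 31, or study day 30 throughout.
- Make the visit 13 window one-sided so that it opens at that cut, for example 0 to +10 days, and count DLTs by onset date. Say how a Doppler finding first seen at that visit is dated, since its onset is not observed.
- State that the committee reviews a cohort only after every patient in it has completed this assessment.
- Reconcile the statement that thirteen visits fall in the first 30 days with the new window.

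Extra DLT assessments at the visits on days 5-9, 14 and 20 are not needed for this. Without Doppler they would not cover the intraportal toxicities in any case.

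The cost is wording and one line of Table 1, with no new visits or imaging. Each hold between cohorts may lengthen by up to about 10 days. The planned 3 to 24 patients do not change.

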**Figure 1 F1:**
[figure not shown]
**Dose-limiting toxicity (DLT) events.**Clinical events of toxicity related to MAPC infusions. If more than one DLT event occurs in a dose cohort, the study will be stopped.

Each patient will receive 2 doses of MAPCs. The first dose will be administered during liver transplantation directly into the portal vein after graft reperfusion. As the study begins with liver transplantation this day is defined as day 1 (in contrast to most preclinical investigation that defines the day of the transplant as "day 0"). The second dose will be administered intravenously on day 3 in the intensive care unit. Three patients will be treated with the starting dose of 2 × 150 million third-party MAPCs. If no DLT is observed in any of the 3 patients of this cohort, the second cohort of 3 patients will be treated with 2 × 300 million MAPCs, continuing with the third cohort with 2 × 450 million MAPCs and the fourth cohort with a final dose of 2 × 600 million MAPCs. The dose escalation design is illustrated in Figure 2.

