**Figure 2 F2:**
[figure not shown]
**Dose escalation design**. Three patients will be treated with the starting dose. If no DLT occurs, the next cohort will be treated with the next MAPC dose level. If one DLT occurs in a cohort, a second cohort of 3 patients will be treated with the same MAPC dose level. The study will be stopped if more than one DLT event is recorded after enrolling at most 6 patients.

Should one patient experience a DLT after 3 patients have been enrolled in any cohort, another 3 patients will be enrolled in the same dose group after consultation with the data safety monitoring board. If no further toxicity occurs, the next 3 patients will be enrolled at the next dose level. If a total of 2 or more patients experience a DLT, either after 3 or 6 patients have been enrolled, the study will be closed and the dose of the previous cohort will be considered the maximum-tolerated dose.

If no toxicities occur at all, the maximum dose administered in the study, i.e., 2 × 600 million MAPCs per patient, will be considered the maximum-tolerated dose and the study will be closed. Using the dose escalation scheme described above, between 3 and 24 patients will be enrolled in this study, with 12 patients being the optimal scenario. The study protocol was designed according to the declaration of Helsinki and approved by the local ethics committee.

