### Dose-Limiting Toxicity

To assess the safety of MAPC infusions, we have defined putative toxicity events anticipated to be specific for stem cell-based therapy in liver transplantation. This dose-limiting toxicity (DLT), which covers specific events that model significant toxicity likely caused by MAPC infusions, is designed as a 'high-barrier score' that aims to detect toxicities of the highest clinical significance that will halt the further development of this therapy option.

The most important consideration is that MAPCs might pool in the first capillary bed after injection and cause micro- or macroembolism. To monitor for potential embolus formation, we have specified diagnostic procedures to examine the liver and lung after intraportal and intravenous injection, respectively. Toxicity related to intraportal infusion will be assessed by Doppler ultrasound determining the maximum portal blood flow, the resistive index (RI) of the hepatic artery, and the presence of any vascular occlusion or changes in the flow patterns. We will monitor lung toxicity by assessing the necessity of reintubation and the occurrence of pulmonary emboli according to published European guidelines after intravenous cell infusion [50]; moreover, the PaO_2_/FiO_2 _ratio [51] will be tightly monitored to detect lung damage. Because MAPCs are derived from a third-party donor and were cultured with bovine serum and recombinant growth factors, MAPC infusion may cause anaphylactic reactions or shock, and systemic toxicity will therefore also be assessed (Figure 1). Three more patients will be enrolled into a dose cohort if one DLT event occurs. The study will be stopped if more than one DLT event occurs after enrolling 6 patients or if the data safety monitoring committee recommends to do so. The feasibility and validity of the DLT events have been validated in 200 retrospectively analyzed patients having received liver grafts without experimental cellular therapy (unpublished data).

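### The stopping and expansion rules count DLT events in some places and patients with a DLT in another, so one patient with two DLT events can either stop the study or only expand the cohort

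*Protocol article*

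**What the plan says.** The stopping rule appears in four places in the protocol article:

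- Figure 1 caption: "If more than one DLT event occurs in a dose cohort, the study will be stopped".
- Figure 2 caption: "The study will be stopped if more than one DLT event is recorded after enrolling at most 6 patients".
- Dose-Limiting Toxicity section: "The study will be stopped if more than one DLT event occurs after enrolling 6 patients", or on the recommendation of the data safety monitoring committee.
- Study Design, text after Figure 2: "If a total of 2 or more patients experience a DLT, either after 3 or 6 patients have been enrolled, the study will be closed". The same sentence makes the previous cohort's dose the maximum-tolerated dose (MTD).

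The expansion rule appears in both units too. The Study Design text says "Should one patient experience a DLT after 3 patients have been enrolled in any cohort, another 3 patients will be enrolled". The Dose-Limiting Toxicity section says "Three more patients will be enrolled into a dose cohort if one DLT event occurs". The Figure 2 caption also expands on one DLT, without naming a unit.

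The DLT window is "within 30 days after administration of the first MAPC dose", and each patient receives two infusions by different routes. The Dose-Limiting Toxicity section lists several signs for each organ. For the lung: "We will monitor lung toxicity by assessing the necessity of reintubation and the occurrence of pulmonary emboli", plus the PaO2/FiO2 ratio. For the liver: portal flow, the resistive index of the hepatic artery, vascular occlusion and changed flow patterns.

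**The concern.** This rule decides the primary endpoint. It determines whether a dose level is passed, expanded or ends the study, and closure fixes the MTD. Events and patients are the same count only if no patient can have more than one countable DLT. With two infusions, a 30-day window and several signs per organ, more than one DLT in a patient looks possible. The article does not say how such a patient would be counted.

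The investigators and the data safety monitoring committee could then reach different decisions from the same data, depending on which statement they apply. The article calls its design a classical 3 + 3, and that design is defined on patients, so the event wording also departs from the design it names.

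**Working it through.** **Stated sample size.** It reproduces: minimum 3 (stop in the first cohort), maximum 4 × 6 = 24, no DLT at all 4 × 3 = 12. These figures are the same under either unit.

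**The four statements side by side.**

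| Statement | Unit | Time point | Case A: 1 of the first 3 patients has two DLT events | Case B: 2 of the first 3 patients have one DLT each |
|---|---|---|---|---|
| Figure 1 caption | events | none stated | stop | stop |
| Figure 2 caption | events | at most 6 enrolled | stop | stop |
| Dose-Limiting Toxicity section | events | 6 enrolled | neither the stop nor the expansion condition is literally met | no stop stated, unless the committee recommends one |
| Study Design text | patients | 3 or 6 enrolled | expand to 6 | close |

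Case A is the conflict of unit. Case B is the conflict of timing, and it is confined to the Dose-Limiting Toxicity section. The Figure 1 caption gives no time point, and the Figure 2 caption's limit of at most 6 is compatible with acting after 3 or 6.

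**Effect on the MTD, by example.** Suppose case A occurs at 2 × 450 million cells. If the event wording stops the study and the Study Design text then names the MTD, the MTD is 2 × 300 million. Under the patient wording, 3 more patients are enrolled at 2 × 450 million. If none of them has a DLT, the study goes on to 2 × 600 million.

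**Illustrative size.** The article gives neither input, so both are assumptions:

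- p, the chance that a patient has at least one DLT, taken as constant over the four levels and independent between patients;
- r, the share of DLT patients who have at least two DLT events.

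Formulas:

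- Pass one level, by patients: (1−p)³ + 3p(1−p)² × (1−p)³
- Pass one level, by events: (1−p)³ + 3p(1−r)(1−p)² × (1−p)³
- Stop before clearing all four levels: 1 − (pass)⁴

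With p = 0.10, (1−p)³ = 0.729 and 3p(1−p)² = 0.243:

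- By patients: 0.729 + 0.243 × 0.729 = 0.906; 1 − 0.906⁴ = 0.326, or 33%.
- By events, r = 0: identical, 33%.
- By events, r = 0.25: 0.729 + 0.75 × 0.177 = 0.862; stop 45%.
- By events, r = 0.50: 0.729 + 0.50 × 0.177 = 0.818; stop 55%.
- By events, r = 0.75: 0.729 + 0.25 × 0.177 = 0.773; stop 64%.

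Over other risks:

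| p | By patients | By events, r = 0 | r = 0.25 | r = 0.50 | r = 0.75 |
|---|---|---|---|---|---|
| 0.05 | 10% | 10% | 20% | 30% | 38% |
| 0.10 | 33% | 33% | 45% | 55% | 64% |
| 0.20 | 75% | 75% | 81% | 86% | 90% |

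The chance that a first group of 3 is exactly case A is 3pr(1−p)². At p = 0.10 this is 6.1% for r = 0.25 and 12.2% for r = 0.50. The chance that at least 2 of the first 3 patients have a DLT, which includes case B, is 3p²(1−p) + p³: 2.8% at p = 0.10 and 10.4% at p = 0.20.

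**The case against.** **Figure 1 may settle the unit.** The DLT definition is in Figure 1, which is not shown. The Dose-Limiting Toxicity section speaks of the DLT as a single construct covering several events and calls it a score. If Figure 1 makes it one composite per patient, a DLT event and a patient with a DLT are the same count. This stands as a condition on the finding. It would not remove the timing gap in the Dose-Limiting Toxicity section.

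**The Study Design text may be meant to govern.** It is the only place that gives expansion, escalation, closure and MTD together. That is a reasonable reading, but the article does not say so, and three other statements use a different unit.

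**Linked DLTs are an inference.** A reader might infer that embolus, reintubation and poor gas exchange would be scored as separate DLTs of one episode. The section lists what is monitored. It does not say that each sign is a separately countable DLT, or at what threshold. Two DLTs in one patient are plausible, but their frequency is unknown.

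**The timing conflict is narrow.** A reader might infer that all four statements clash on timing, or that the Dose-Limiting Toxicity section tells the team to carry on after two DLTs in 3 patients. Neither is supported. That section is incomplete for the case and does not instruct continuation. The committee reviews each cohort to day 30 and may recommend stopping at any time. This limits the safety consequence but does not say which count applies.

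**The event wording is the cautious one.** Where the event count and the patient count differ at the same look, the event count stops sooner. That is true, but the decision and possibly the MTD still differ for the same data.

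**Conclusion.** The concern holds as an internal contradiction in the trial's primary decision rule. Three statements stop on more than one DLT event and one closes on 2 or more patients with a DLT. The expansion rule is worded in both units as well. One patient with two DLT events among the first 3 gives opposite decisions, subject to the condition that Figure 1 does not define a per-patient composite. Whatever Figure 1 contains, the Dose-Limiting Toxicity section states no event-based stop for two DLTs among the first 3, whereas the Study Design text closes the study there if they are in two patients.

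The contradiction rests on the wording alone. The percentages (33% by patients against 33% to 64% by events at 10% risk) rest on an assumed constant risk and an assumed share of patients with several events, and the difference vanishes when that share is zero. They show how sensitive the design is to the counting unit and should not be read as an expected effect in this trial. The range of 3 to 24 patients and the 12-patient scenario are unaffected.

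**What to change.** Reconcile the two figure captions, the Dose-Limiting Toxicity section and the Study Design text to one counting unit and one set of time points, for both the stopping and the expansion rule. State explicitly how several DLT events in one patient are counted, and check that the definition in Figure 1 agrees. State what happens when the stopping count is reached within the first 3 patients, so that no statement leaves that case open.

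The classical 3 + 3 design that the article names is defined on patients, which the sponsor should bear in mind. The choice of stopping rule remains the sponsor's, in consultation with the data safety monitoring committee.

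The cost is a wording amendment. It needs no added patients, visits or procedures.
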